# Protocol for a case–control diagnostic accuracy study to develop diagnostic criteria for psoriasis in children (DIPSOC study): a multicentre study recruiting in UK paediatric dermatology clinics

**DOI:** 10.1136/bmjopen-2018-028689

**Published:** 2019-08-27

**Keywords:** psoriasis children diagnosis case-control

## Abstract

**Introduction:**

Diagnosing psoriasis in children can be challenging. Early and accurate diagnosis is important to ensure patients receive psoriasis specific treatment and monitoring. It is recognised that the physical, psychological, quality of life, financial and comorbid burden of psoriasis are significant. The aim of this study is to develop clinical examination and history-based diagnostic criteria for psoriasis in children to help differentiate psoriasis from other scaly inflammatory rashes. The criteria tested in this study were developed through a consensus study with a group of international psoriasis experts (International Psoriasis Council).

**Methods and analysis:**

Children and young people (<18 years) with psoriasis (cases) and other scaly inflammatory skin diseases (controls) diagnosed by a dermatologist are eligible for recruitment. All participants complete a single research visit including a diagnostic criteria assessment by a trained investigator blinded to the participant’s diagnosis. The reference standard of a dermatologist’s diagnosis is extracted from the medical record. Sensitivity and specificity of the consensus derived diagnostic criteria will be calculated and the best predictive criteria developed using multivariate logistic regression.

**Ethics and dissemination:**

Health Regulatory Authority and National Health Service Research Ethics Committee approvals were granted in February 2017 (REC Ref: 17/EM/0035). Dissemination will be guided by stakeholders; patients, children and young people, dermatologists, primary care and paediatric rheumatologists. The aim is to publish the study results in a high-quality peer-reviewed journal, present the findings at international academic meetings and disseminate more widely through social media and working with patient associations.

**Trial registration number:**

ISRCTN98851260.

Strengths and limitations of this studyThis is a UK multicentre study recruiting 320 consecutive children and young people in 12 paediatric dermatology departments.The trained investigator undertaking the diagnostic criteria assessment is blinded to the participant’s reference standard of a dermatologist’s diagnosis.A case–control study design is likely to overestimate the diagnostic accuracy, but this is an appropriate and feasible study design for a diagnostic criteria development study.External validation of the diagnostic criteria will be needed in the setting and population that the criteria will be used.

## Introduction

Psoriasis is a chronic immune-mediated inflammatory disease of the skin and joints.^1 2^ It is recognised by the World Health Organisation (WHO) as a serious non-communicable disease and an area of unmet health need.^3^ Although the exact causes for the onset of psoriasis are not fully understood, they originate in a complex interaction between genetic and environmental factors.^4^ Psoriasis can affect the face, hands, nails, genitals and flexures, therefore, it is both the extent and the location of disease that are important to patients. It is known that the physical, psychological, quality of life, financial and comorbid burden of psoriasis are significant.^5–11^

Psoriasis can affect people of all ages. However, making the diagnosis in children and young people can be more challenging compared with diagnosing psoriasis in adults. Psoriasis is often under-recognised in this younger age group and may be misdiagnosed as other common red scaly rashes such as eczema, viral exanthems and fungal infections. The clinical features seen in childhood disease are often more subtle with thinner plaques, facial involvement and flexural disease in hidden sites normally covered by clothing.^12–14^ Therefore, the diagnosis of psoriasis in children and young people may be missed by non-dermatologists.

Epidemiological data are limited, but it is estimated that one-third of adults with psoriasis first develop skin changes in childhood.^15 16^ Therefore, early and accurate diagnosis presents an opportunity for early intervention. National Institute for Health and Care Excellence (NICE) recommends all children with suspected psoriasis are referred to a dermatology specialist for assessment and management.^17^ This specialist review also includes initiating monitoring for comorbid diseases and assessment for juvenile psoriatic arthritis. Accurate recognition of psoriasis is also important to help paediatric rheumatologists differentiate juvenile idiopathic arthritis into juvenile psoriatic arthritis. This differentiation alters the treatment pathway and likely prognosis for children with juvenile psoriatic arthritis.^18^ Ensuring children and young people receive psoriasis specific treatment and monitoring from the onset is important to help minimise the negative long-term consequences of psoriasis, known as cumulative life course impairment.^19^

There are no clinical examination-based diagnostic criteria for psoriasis.^20^ Diagnosis in clinical practice currently relies on expert pattern recognition by a trained dermatologist.^21 22^ Skin biopsies are not routinely taken, especially in children. Consequently, there are no available diagnostic aids to support non-dermatologists to recognise psoriasis in children. In research studies, the case-definition and eligibility criteria for psoriasis in children are often poorly described, reducing the generalisability and ability to synthesis studies.^23 24^

Improving awareness of psoriasis has been identified as a topic of importance in the Psoriasis and Psoriatic Arthritis Alliance (PAPAA) prioritisation exercise. The recently completed James Lind Alliance Psoriasis Priority Setting Partnership (PSP) identified 10 research priorities in psoriasis that are important to people who have psoriasis, their families and friends, and the healthcare professionals who treat them. The second priority asks ‘Does treating psoriasis early (or proactively) reduce the severity of the disease, make it more likely to go into remission, or stop other health conditions developing’.^25^ In children and young people, ensuring early and accurate recognition of psoriasis will be a necessary part of answering this question.

An initial eDelphi consensus study has been completed with a group of global clinically active psoriasis experts who are members of the International Psoriasis Council. The group agreed 16 clinical features that are important for the diagnosis of plaque psoriasis in children.^26^

The next step in developing diagnostic criteria for psoriasis in children is to empirically test how well the consensus-derived diagnostic criteria perform and to refine the criteria. The Developing **DI**agnostic criteria for **PSO**riasis in **C**hildren (DIPSOC) study has been designed to develop a diagnostic tool for identifying childhood psoriasis. The primary objective is to test the diagnostic accuracy (sensitivity and specificity) of the consensus agreed diagnostic criteria (box 1) and develop the best predictive diagnostic criteria using multivariate analysis. DIPSOC is a development study because further validation work is needed before the diagnostic accuracy of the criteria in primary, secondary and research settings are known.

Box 1Sixteen diagnostic features agreed by the International Psoriasis Council to be important for the diagnosis of plaque psoriasis in children (26). Two additional diagnostic features (*) have also been included that were close to reaching consensus and were emphasised as important in the feedback from experts.Major criteriaScaly erythematous plaques on the extensor surfaces of the elbows and knees.Scaly erythematous plaques on the trunk triggered by a sore throat or other infection.Raindrop plaques typical of guttate disease on the trunk or limbs.Minor criteriaScale and erythema in the scalp involving the hairline.Retroauricular erythema (including behind the earlobes).Scaly erythema inside the external auditory meatus.Persistent well-demarcated erythematous scaly rash anywhere on the body.Fine scaly patches involving the upper thighs and buttocks.Well-demarcated erythematous rash in the napkin area involving the crural folds.Persistent erythema in the umbilicus.Nail pitting.Onycholysis of the nail(s).Subungual hyperkeratosis of the nail(s).Positive family history of psoriasis.Koebner phenomenon.Fusiform swelling of a toe or a finger suggestive of dactylitis.*Persistent well-demarcated facial rash with fine or absent scale.*Natal cleft erythema and/or skin splitting.

## Methods

### Study design

DIPSOC is a multicentre case–control diagnostic accuracy study with a nested substudy. The nested substudy is recruiting children and young people with indeterminate psoriasis alongside the main study. The full protocol was lodged on the Centre of Evidence Based Dermatology website prior to the first participant being recruited. This published protocol is based on Protocol 12.10.2017 Final V.1.2. The full protocol is available on the Centre of Evidence Based Dermatology University of Nottingham website www.nottingham.ac.uk/go/dipsoc.

### Primary objective

To test the diagnostic accuracy of the consensus agreed diagnostic criteria for plaque psoriasis in children/young people and develop the best predictive diagnostic criteria using multivariate analysis.

### Secondary objectives

To compare the diagnostic performance of the consensus agreed diagnostic criteria and the best predictive criteria for plaque psoriasis in children and young people.To assess the interobserver variability in the diagnostic criteria assessment.To assess the variability in the reference standard for psoriasis.

### Setting

DIPSOC is recruiting in 12 UK paediatric dermatology outpatient clinics in secondary and tertiary care. This setting is a feasible environment in which the reference standard (dermatologist’s diagnosis) can be obtained and the sample size recruited within the time and resources available. A specialist setting is appropriate for a development study, but validation research will be needed to test the performance of the diagnostic criteria in the settings that they are intended to be used (eg, primary care and paediatric rheumatology clinics).

### Participant selection

#### Inclusion criteria

Cases and controls are children and young people aged 0 to <18 years, with active skin disease (rash present) at the time of assessment and are able to consent or have a parent/guardian willing to give consent.

Cases have a confirmed diagnosis of plaque psoriasis by a dermatologist. Plaque psoriasis has been used as a broad term to include all subtypes and presentations of psoriasis where plaques are the main feature. For example, chronic plaque psoriasis, guttate psoriasis, scalp psoriasis and flexural psoriasis are included but purely nail psoriasis or juvenile psoriatic arthritis without skin involvement are excluded. The decision to include guttate psoriasis under the broad description of plaque psoriasis was agreed with the International Psoriasis Council.

Controls have a confirmed diagnosis of a scaly inflammatory rash (excluding psoriasis or indeterminate psoriasis) by a dermatologist. Skin conditions that may be included in the control population are eczema (atopic dermatitis), pityriasis rubra pilaris, pityriasis rosea, ichthyosis, mycosis fungoides, Gianotti-Crosti and tinea corporis. These conditions are not an exhaustive list and the decision as to whether a participant’s skin disease meets the eligibility criteria is made by the patient’s dermatologist.

#### Exclusion criteria

Children or young people with pustular psoriasis, erythrodermic psoriasis or do not have a dermatologist’s diagnosis.

### Index test

A diagnostic criteria assessment looking for the presence or absence of each of the diagnostic features (box 1). Using the same assessment, the index test is divided into index test 1 and index test 2.

#### Index test 1

The international eDelphi consensus study agreed 16 diagnostic features of childhood psoriasis and separated them into major and minor criteria. In the consensus study, a scoring algorithm was proposed where the presence of one or more major criteria or three of more minor criteria would support a diagnosis of psoriasis. Together these 16 diagnostic features and the scoring algorithm form index test 1.^26^

#### Index test 2

Two additional features were close to reaching consensus and were emphasised as important in the feedback from the expert participants. These 18 items will be used to create the best predictive criteria using multivariate analysis. The best predictive criteria form index test 2.

### Reference test

A dermatologist’s diagnosis as recorded in the participant’s medical record. The diagnosis is a clinical diagnosis and may include, but does not require, a skin biopsy.

### Study flow

The study flow is depicted in figure 1. Children and young people who meet the eligibility criteria to be a case or control are approached by their usual dermatology team. They are invited to attend a research visit on the same day, at their next consultation or at a separate research visit. All consecutive psoriasis patients are being approached and consecutive control patients when a case is identified. Cases identified from existing medical records are approached by letter from their usual dermatology team.

**Figure 1 F1:**
[figure not shown]
Developing DIagnostic criteria for PSOriasis in children study flow. CRN, Clinical Research Network.

After informed consent has been taken, all participants undergo the same research visit. The visit comprises demographic questions, quality of life questionnaires (for those aged 4–17 years) and a diagnostic criteria assessment by a study investigator who is blinded to the participant’s diagnosis (blinded to the reference standard). The two quality of life questionnaires are the Children’s Dermatology Life Quality Index and the Child Health Utility 9D.

Each participant is offered a certificate, sticker and voucher to say thank you for taking part. Following the research visit, information is extracted from the medical record by an investigator who did not perform the assessment (blinded to the index test). Data to be extracted include the reference standard (diagnosis of skin disease), duration of disease, disease severity and current treatments. A summary of the data variables collected in the DIPSOC study is presented in box 2.

Box 2A summary of the data variables collected in the DIPSOC studyResearch visitDemographic information: age, sex, ethnicity, household occupation.Diagnostic criteria assessment: presence and absence of each of the 18 diagnostic features (index test).Clinical experience of the diagnostic criteria assessor.Unblinding of the diagnostic criteria assessor.Quality of life questionnaires (4–17 years)—CDLQI and CHU-9D.Contact details (optional consent).Medical recordParticipant’s diagnosis (reference standard).Age at diagnosis.Age at onset of symptoms.Skin biopsy result.Disease severity.Presence of psoriatic arthritis.Current skin treatments—topical, systemic, phototherapy.Clinical photographs (optional consent).CDLQI, Children’s Dermatology Life Quality Index; CHU-9D, Child Health Utility 9D; DIPSOC, Developing DIagnostic criteria for PSOriasis in Children.

### Data management

Data are collected at the time of assessment and from the medical record. A number of steps have been taken to help ensure high-quality data collection. All DIPSOC study investigators undergo standardised training and receive a study manual to use as a practical guide when conducting the study. All DIPSOC diagnostic criteria assessors are trained using a PowerPoint presentation by [name] (a clinical dermatologist with an interest in paediatric psoriasis) either face to face or by teleconference. Diagnostic criteria assessors come from both a dermatology and non-dermatology background. Understanding of the training material is checked using a short assessment based on clinical photographs. All assessors are required to achieve a minimum of 90% in the assessment prior to starting the study. The diagnostic criteria training manual is provided as a reference aid for investigators to use during their assessment.

The case report form includes guidance notes and was piloted to check for accuracy of completion. Quality of life is measured using validated measurement instruments. A data management process has been designed to minimise errors. All data monitoring is taking place centrally and data queries are checked with individual recruiting sites. Data checks are also built into the database design and all data for the primary objective will be entered twice.

### Consistency checks

To assess the interobserver variability in the diagnostic criteria assessment, the assessment will be conducted consecutively by two independent assessors in the first forty participants where two assessors are available.

To assess the variability in the reference standard for psoriasis, when optional consent is given, anonymised clinical photographs of cases taken as part of routine clinical care will be sent as anonymised case studies to the twelve consultant dermatologist principal investigators. The consultant dermatologists will be asked to score whether they agree or disagree with the diagnosis of psoriasis.

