### Sample size and data analysis

The sample size is based on the primary objective. First, based on a 95% CI that the positive likelihood ratio (LR) is greater than 2 assuming a ratio of 1:1 cases to controls and an estimated sensitivity of 0.8 and specificity of 0.7 the sample size required is 74 cases and 74 controls.^27^

Second, transparent reporting of multivariable prediction models for individual prognosis or diagnosis (TRIPOD) has stated that there are no clear methods for calculating an adequate sample size. The guidance supports the current rule of thumb for sample size calculations of 10 events per variable.^28^ As there are 16 diagnostic features in the consensus agreed diagnostic criteria, a sample size of 160 cases and 160 controls has been calculated.

Participant characteristics will be analysed using descriptive statistics. The diagnostic accuracy of the consensus agreed criteria will be calculated using sensitivity and specificity; 95% CIs will be presented. Multivariate logistic regression analysis will be used to develop the best predictive criteria using the DIPSOC data. The diagnostic features will be entered into the backward regression model. All minor criteria will be entered into the regression model and LR will be presented. Variation of diagnostic accuracy in different clinical contexts will be explored in stratified analysis for the following variables; age at the time of assessment, sex, assessor type and consultation type (new or follow-up).

The results of the multivariate analysis will be plotted on a receiver operator characteristic (ROC) curve and a coefficient threshold determined. The minimum threshold for the best predictive criteria has been set at 0.8 sensitivity and 0.8 specificity after consultation with the expert advisory group (detailed in the acknowledgements). The best predictive diagnostic criteria will be applied to the study data and sensitivity and specificity calculated. The performance of the consensus agreed criteria and the best predictive model criteria will be compared using area under the ROC curve.

Interobserver variability and variability in the reference standard will be calculated using the kappa statistic. Further details on the analysis will be made public in the statistical analysis plan which will be shared on the DIPSOC website www.nottingham.ac.uk/go/dipsoc before the end of recruitment.

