### Minimising bias

We have minimised selection bias by asking sites to approach all eligible cases and consecutive controls. All those approached but not recruited will be included in a screening log to demonstrate a non-selective approach. By minimising exclusion criteria, we aimed to design an inclusive study to support generalisation of the results.

The diagnostic criteria assessment will be undertaken by an investigator who is unaware of (blinded to) the dermatologist’s diagnosis of the participant. Investigators are trained to focus on the presence or absence of each clinical feature. The study will test a prespecified scoring algorithm proposed through the eDelphi consensus study and a prespecified diagnostic threshold decided with the expert advisory group.

Bias in the reference standard will be minimised by ensuring all participants have a confirmed diagnosis by a dermatologist. As this is a case–control study, the reference standard will predate the index test. Variability in the reference standard will be examined using clinical photographs.

We have designed the study to include same day recruitment directly from clinic, therefore, the time between the reference standard and index test for most participants will be short. All participants receive the same reference standard (a dermatologist’s diagnosis), therefore, complete verification will be achieved. All participants will be included within the analysis and a complete data set sensitivity analysis is planned. Data are extracted from the medical record by an investigator who did not undertake the diagnostic criteria assessment (blinded to the index test).

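### Variability in the reference standard is to be summarised by kappa on photographs of cases only, which yields a zero or strongly depressed coefficient and leaves control diagnoses unchecked

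*Protocol article*

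**What the plan says.** The third secondary objective is "To assess the variability in the reference standard for psoriasis". The Consistency checks section supplies the method: with optional consent, "anonymised clinical photographs of cases taken as part of routine clinical care will be sent as anonymised case studies", and these go "to the twelve consultant dermatologist principal investigators". The raters are then "asked to score whether they agree or disagree with the diagnosis of psoriasis". The Inclusion criteria define the photographed group: "Cases have a confirmed diagnosis of plaque psoriasis by a dermatologist".

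Sample size and data analysis fixes the statistic: "Interobserver variability and variability in the reference standard will be calculated using the kappa statistic". It does not say whether kappa compares each rater with the medical record or the raters with one another, and it leaves further analysis detail to the statistical analysis plan.

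Minimising bias describes the exercise without restricting it to cases: "Variability in the reference standard will be examined using clinical photographs". Nothing else in the article re-examines a control's diagnosis. The two-assessor check in the first forty participants concerns the index test, and the substudy concerns indeterminate psoriasis.

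**The concern.** Kappa corrects observed agreement for chance agreement, and chance agreement depends on how the ratings divide between categories. Where nearly every image belongs in one category, chance agreement is close to observed agreement and little room is left for kappa to exceed zero, however competent the raters are. Sampling cases only creates that situation.

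Two things are at stake. First, a low kappa would be read in the usual way, as evidence that dermatologists do not agree on psoriasis in children, when it may reflect only the composition of the image set. Second, sensitivity and specificity both rest on the recorded diagnosis, but the check covers only the group that determines sensitivity. A control who truly has psoriasis and meets the criteria is counted as a false positive, which lowers apparent specificity. The Introduction says that childhood psoriasis can be mistaken for eczema, and eczema is the first control condition named in the Inclusion criteria. The Introduction's point is mainly about non-dermatologists, so it shows what kind of error is plausible and not how often it occurs in these clinics.

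**Working it through.** The article gives no target kappa, precision or number of photographs for this check, so there is no planned figure to reproduce.

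**Inputs from the article:** cases only, so the recorded diagnosis is constant; 12 raters; a binary agree/disagree score; at most 160 photographed cases, since 160 cases is the sample size and photographs need optional consent. **Assumed:** rater behaviour, for which the article gives no figure.

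**Formula:** kappa = (Po − Pe)/(1 − Pe), where Po is observed agreement and Pe is chance agreement.

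**Reading 1: each rater against the record.** Let a rater agree with a proportion p of the diagnoses. The record says psoriasis every time, so Po = p and Pe = 1 × p + 0 × (1 − p) = p. The numerator is zero for every p.

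- 152 of 160 agreed: Po = Pe = 0.95, kappa = 0/0.05 = 0.
- 32 of 160 agreed: Po = Pe = 0.20, kappa = 0/0.80 = 0.
- 160 of 160 agreed: Po = Pe = 1, kappa = 0/0, undefined.

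This is algebra and needs no assumption about the raters. With 160 controls added and the same accuracy in both groups, Pe = 0.5, and accuracies of 0.95, 0.90 and 0.80 give kappa of 0.90, 0.80 and 0.60.

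**Reading 2: among the twelve raters.** Suppose 90% of case images are clear (each rater says psoriasis with probability 0.95) and 10% are hard (probability 0.50).

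- Overall proportion scored psoriasis: 0.9 × 0.95 + 0.1 × 0.50 = 0.905.
- Po = 0.9 × (0.95² + 0.05²) + 0.1 × (0.5² + 0.5²) = 0.8145 + 0.05 = 0.8645.
- Pe = 0.905² + 0.095² = 0.828.
- kappa = (0.8645 − 0.828)/(1 − 0.828) = 0.21.

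Add an equal number of controls whose clear and hard images mirror those of the cases. Po is unchanged at 0.8645, Pe falls to 0.5, and kappa = 0.3645/0.5 = 0.73. If instead all case images are equally clear at 0.90, then Po = 0.9² + 0.1² = 0.82 = Pe, and the expected kappa is 0.

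**Range under a second model.** Let every rater have sensitivity and specificity s, and let a share π of the images be truly psoriasis. Then Po = s² + (1 − s)², the proportion scored psoriasis is q = πs + (1 − π)(1 − s), and Pe = q² + (1 − q)².

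| s | Pairwise agreement | π = 1.00 | π = 0.98 | π = 0.95 | π = 0.90 | π = 0.50 |
|---|---|---|---|---|---|---|
| 0.95 | 0.905 | 0.00 | 0.25 | 0.45 | 0.61 | 0.81 |
| 0.90 | 0.820 | 0.00 | 0.12 | 0.25 | 0.39 | 0.64 |
| 0.85 | 0.745 | 0.00 | 0.07 | 0.15 | 0.26 | 0.49 |

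Within each row rater skill and pairwise agreement are fixed; only the image mix changes. In 500 simulated exercises with 160 images, 12 raters and s = 0.90, the central 95% of kappa values ran from 0.11 to 0.36 at π = 0.95 and from 0.60 to 0.68 at π = 0.50.

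**The case against.** A reader might infer that kappa is zero by construction under any analysis. The article does not support that, because it does not name the comparator. With twelve raters, a multi-rater kappa is at least as natural a reading of variability, and that coefficient can be estimated and does vary with the data: 0.25 to 0.61 at s = 0.95 when 98% to 90% of images are truly psoriasis. The forced zero belongs to Reading 1 only.

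A reader might also infer that the secondary objective cannot be met. That goes too far. The agree/disagree scores give the proportion of case diagnoses confirmed, which partly answers the objective, and the objective's wording can be read as concerning psoriasis diagnoses alone. Nor does it follow that investigators will score their own patients: the article does not say how the anonymised case studies are allocated. That raters see the recorded diagnosis is a reasonable inference from the agree/disagree task, but the presentation is not described.

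The kappa type and companion agreement measures properly belong in the statistical analysis plan, and their absence here is not a fault. The check is secondary, and nothing in the stated analysis feeds its result into the accuracy estimates, the model or the threshold.

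Two things survive all of this. The article itself pairs kappa with a cases-only sample, and an analysis plan can refine the coefficient but cannot supply control photographs that the design does not send to the raters.

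**Conclusion.** The point holds as a weakness of one secondary check and should be corrected; the primary accuracy analysis can still be run. Against the record, kappa carries no information: 95% and 20% agreement both give 0. Among the raters it is depressed and hard to interpret: about 0.2 rather than about 0.7 in the first illustration, and 0.12 to 0.39 rather than 0.64 at s = 0.90 with 98% to 90% of images truly psoriasis. The Reading 1 result needs no assumption. The Reading 2 figures rest on assumed rater behaviour and, for the balanced comparison, on controls being as easy to judge as cases; they show how kappa depends on the mix and do not predict this study's value. Separately, errors in control diagnoses are not examined, although Minimising bias presents the photograph exercise as covering the reference standard generally.

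**What to change.** Where consented routine photographs of controls exist, mix them with the case photographs in random order and mask the recorded diagnosis. Box 2 lists clinical photographs under optional consent without limiting them to cases. Ask each rater for psoriasis, not psoriasis or cannot tell, state in advance how the third answer is handled, name the comparator for kappa, and report kappa with positive and negative agreement. The same twelve raters can do this. The cost is more images per rater, or fewer case images for the same workload. The article does not show how many control photographs are available, so this should be established first.

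If control photographs are not available, replace kappa with the proportion of case diagnoses confirmed and a 95% CI that allows for the same raters scoring many images, and state that control diagnoses were not checked. This needs no new data. In that event, the sentence in Minimising bias should be narrowed to say that variability was examined among cases only.

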### Study progress

Twelve UK centres are open for recruitment. These centres are Nottingham, Barts London, Middlesbrough, Cambridge, Sheffield, Coventry, Glasgow, Dorchester, Oxford, St George’s London, Plymouth and Cardiff. The first participant was recruited in October 2017 and the study is due to finish recruiting on August 2019. We are currently in the data collection phase.

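### The photograph check of the reference standard appears to include the principal investigator of each case's own clinic, so about one rating in twelve is not independent of the diagnosis being checked

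*Protocol article*

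**What the plan says.** One secondary objective is to assess variability in the reference standard for psoriasis. The reference standard itself is defined under Reference test as "A dermatologist’s diagnosis as recorded in the participant’s medical record".

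Under Consistency checks, the material to be rated is "anonymised clinical photographs of cases taken as part of routine clinical care", used "when optional consent is given". These photographs "will be sent as anonymised case studies to the twelve consultant dermatologist principal investigators". The task is fixed as follows: "The consultant dermatologists will be asked to score whether they agree or disagree with the diagnosis of psoriasis".

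Under Sample size and data analysis the statistic is named: "Interobserver variability and variability in the reference standard will be calculated using the kappa statistic". The form of kappa is not given there, and further analysis detail is deferred to the SAP.

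Two other sections show who the raters are in relation to the cases. Study progress states "Twelve UK centres are open for recruitment" and lists the centres. Study flow says that eligible children "are approached by their usual dermatology team". The article nowhere says that an investigator is kept from rating cases from their own centre.

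**The concern.** A check on the reproducibility of a diagnosis should use raters who had no part in making it. With twelve principal investigators and twelve centres, the panel for each rated case appears to include the consultant who leads the study at the clinic where the child was diagnosed. That consultant may have made the diagnosis, may know it from the clinic, or may recognise the rash or the clinic photograph. Anonymising removes identifiers but cannot rule out recognition.

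The article protects independence elsewhere. The interobserver check of the index test calls for two independent assessors, and the medical record is extracted by someone who did not do the assessment. The reference-standard check has no comparable separation. Yet it serves a named secondary objective, and the Minimising bias section cites it in discussing bias in the reference standard. At stake is how far the reported agreement reflects independent dermatologists.

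**Working it through.** The article gives no figure for this check, so there is none to reproduce.

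**Inputs**

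- Raters: 12 (Consistency checks). Centres: 12 (Study progress). One investigator per centre is inferred from the matching numbers.
- All twelve score every rated case: the plain reading of Consistency checks.
- *p*, the probability that an off-site rater agrees with the diagnosis: not in the article, assumed 0.6 to 0.95.
- κ, the multi-rater (Fleiss) kappa among the eleven off-site raters: not in the article, assumed 0.2 to 0.6.
- The own-site investigator always agrees: a worst-case assumption.

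**Step 1. Share of non-independent ratings**

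Own-site ratings: 1/12 = 8.3%. Rater pairs per case: 12 × 11 / 2 = 66, of which 11 include the own-site rater, so 11/66 = 16.7%. The overall 1/12 does not depend on how recruitment is spread over centres. The share for an individual rater does: if a centre supplied 30% of the photographs (an assumption), 30% of its investigator's ratings would be own-site.

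**Step 2. Percent agreement with the diagnosis**

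Reported agreement = (11*p* + 1)/12, so the shift is (1 − *p*)/12.

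| *p* among the eleven | Reported with twelve | Shift (points) |
|---|---|---|
| 0.60 | 63.3% | 3.3 |
| 0.70 | 72.5% | 2.5 |
| 0.80 | 81.7% | 1.7 |
| 0.90 | 90.8% | 0.8 |
| 0.95 | 95.4% | 0.4 |

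**Step 3. Kappa**

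The article plans kappa. I take a multi-rater form, because every rated case already carries a psoriasis diagnosis and a kappa against that constant would be zero or undefined.

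- Two off-site raters disagree with probability 2*p*(1 − *p*)(1 − κ).
- The own-site rater and an off-site rater disagree with probability 1 − *p*.
- Mean pairwise disagreement: D = [55 × 2*p*(1 − *p*)(1 − κ) + 11(1 − *p*)]/66.
- Chance disagreement: E = 2*m*(1 − *m*), with *m* = (11*p* + 1)/12.
- Kappa with twelve raters = 1 − D/E.

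For *p* = 0.80 and κ = 0.40:

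- Off-site pairs: 2 × 0.8 × 0.2 × 0.6 = 0.192.
- D = (55 × 0.192 + 11 × 0.20)/66 = 12.76/66 = 0.193.
- E = 2 × 0.8167 × 0.1833 = 0.299.
- Kappa = 1 − 0.1933/0.2994 = 0.354.

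The same formula over the assumed range, which a simulation of 200,000 cases per scenario matches closely:

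| *p* | κ 0.20 becomes | κ 0.40 becomes | κ 0.60 becomes |
|---|---|---|---|
| 0.70 | 0.17 | 0.35 | 0.52 |
| 0.80 | 0.18 | 0.35 | 0.53 |
| 0.90 | 0.18 | 0.36 | 0.54 |

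Kappa falls because a rater who always agrees does not follow the case-to-case variation seen by the other eleven, while the higher mean also raises the agreement expected by chance.

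**The case against.** Four arguments stand against the point.

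*The effect is small and its direction is not fixed.* This stands. A reader might infer that own-site ratings always flatter the reference standard. That holds for percent agreement only. Under the worst-case assumption a multi-rater kappa is lowered, and the article plans kappa without naming its form. No claim of a consistently favourable bias is supported.

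*The main results do not use these ratings.* This also stands. A reader might infer that every sensitivity and specificity figure is compromised. Those figures use the diagnosis in the medical record, and nothing from the photograph check enters them, the model or the threshold. What is affected is the evidence on how variable that diagnosis is.

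*The chain is inferred.* Partly right. The article does not say that the investigator made the diagnosis, only that a dermatologist did. Nor does it say that anonymised photographs will be recognised, and the check covers only cases with optional consent and routine photographs, not every case. It would be wrong to state as fact that clinicians confirm their own diagnoses. The inference of one investigator per centre is nevertheless strong, and the possibility of non-independence is enough to justify a safeguard.

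*An exclusion may sit in the full protocol or the SAP.* Possible, since neither is shown. But the article does not merely stay silent on the panel: it names all twelve investigators as recipients, which is a matter of study conduct. If an exclusion exists elsewhere, one clause would bring this section into line.

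**Conclusion.** The point holds as a minor one. On the natural reading, 8.3% of ratings and 16.7% of rater pairs per rated case involve the principal investigator of the diagnosing clinic, and the article states no step to separate them. In the worst case, percent agreement rises by up to about 3 points for *p* of 0.6 or more, and a multi-rater kappa falls by about 0.02 to 0.08 over the assumed range. This is a modest distortion of a secondary result, in a direction that depends on the statistic.

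The conclusion rests on one investigator per centre, on all twelve rating each rated case, and on the own-site investigator always agreeing. If own-site investigators do not recognise their patients and rate as the others do, the distortion disappears.

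**What to change.** Add one sentence under Consistency checks: a case is not sent to the principal investigator of its own recruiting site. If photographs have already gone to all twelve, record the recruiting site of each case, drop own-site ratings from the primary agreement analysis, and report kappa and percent agreement with and without them.

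The cost is a site filter and one rating in twelve, leaving eleven per case and a small loss of precision. Because the omitted rater differs by site, the kappa chosen must allow the set of raters to vary between cases.
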